### **5. PATIENT WITHDRAWAL CRITERIA**

Patients will be excluded from further assessment if there is withdrawal of informed consent. Severe adverse events related to the study drug are also a reason for withdrawal from the study drug but not withdrawal from study follow-up.

### **6. PROTOCOL VIOLATIONS**

A protocol violation occurs when an event happens that does not allow for accurate interpretation of response to treatment. Protocol violations will be defined in the statistical analysis plan. All patients should be followed up until the end of the passive follow up unless fulfilling the study withdrawal criteria.

### **7. SAFETY VARIABLES**

Safety and tolerability of the treatments will be evaluated by recording Adverse Events (AEs) and grading, laboratory, and vital signs evaluations.

#### **7.1 Adverse Events**

At each visit, the Investigator will ascertain the occurrence of any adverse events since the last visit. Any event must be recorded on the CRF.

##### **7.1.1 Definition of an adverse event**

An AE is any untoward medical occurrence in a patient or clinical investigation subject administered a pharmaceutical product and which does not necessarily have a causal relationship with this treatment.

An AE can therefore be any unfavourable and unintended sign (that could include a clinically significant abnormal laboratory finding), symptom or disease temporally associated with the use of a medicinal product, whether or not considered related to the medicinal product.

#### **7.1.2 Severity, relationship of event to study drug, and outcome**

The severity of a clinical adverse event is to be scored according to the following scale:

|   |                  |                                                                 |
|---|------------------|-----------------------------------------------------------------|
| 1 | Mild             | Awareness of sign or symptom, but easily tolerated              |
| 2 | Moderate         | Discomfort enough to cause interference with usual activity     |
| 3 | Severe           | Incapacitating with inability to work or perform usual activity |
| 4 | Life-threatening | Patients at risk of death at the time of the event              |

The relationship of an adverse event to study drug is to be assessed according to the following definitions:

- 1      **Definitely unrelated**  
Should be reserved for those events which occur prior to test drug administration (e.g., washout or single-blind placebo) or for those events which cannot be even remotely related to study participation (e.g. injury caused by a third party).
- 2      **Unlikely**  
There is no reasonable temporal association between the study drug and the suspected event and the event could have been produced by the subject's clinical state or other modes of therapy administered to the subject.
- 3      **Possible**  
The suspected adverse event may or may not follow a reasonable temporal sequence from study drug administration but seems to be the type of reaction that cannot be dismissed as unlikely. The event could have been produced or mimicked by the subject's clinical state or by other modes of therapy concomitantly administered to the subject.
- 4      **Probable**  
The suspected adverse event follows a reasonable temporal sequence from study drug administration, abates upon discontinuation of the drug, and cannot be reasonably explained by the known characteristics of the subject's clinical state.
- 5      **Definitely related**  
Should be reserved for those events which have no uncertainty in their relationship to test drug administration: this means that a rechallenge was positive.

The outcome of each AE must be assessed according to the following classification:

|                                  |                                                                                                         |
|----------------------------------|---------------------------------------------------------------------------------------------------------|
| - completely recovered :         | The patient has fully recovered with no observable residual effects                                     |
| - not yet completely recovered : | Improvement in the patient's condition has occurred, but the patient still has some residual effects    |
| - deterioration :                | The patient's overall condition has worsened                                                            |
| - permanent damage :             | The AE has resulted in a permanent impairment                                                           |
| - death :                        | The patient died due to the AE                                                                          |
| - ongoing :                      | The AE has not resolved and remains the same as at onset                                                |
| - unknown :                      | The outcome of the AE is not known because the patient did not return for follow-up (lost to follow-up) |

### **7.1.3 Definition of a serious adverse event**

A serious adverse event (experience) (SAE) or reaction is any untoward medical occurrence that at any dose fulfils at least one of the following criteria:

- \* results in death;
- \* is life-threatening;
- \* requires hospitalization (other than for drug administration) or prolongation of existing hospitalization;
- \* results in persistent or significant disability/incapacity;
- \* requires a specific medical or surgical intervention to prevent one of the outcomes listed above;

**All serious adverse events, whether or not deemed drug-related, or expected, must be reported immediately or within 24 hours (one working day), using the Serious Adverse Event Notification Form , by telefax or email to :**

The chairman of the IRB  
Institute of Tropical Medicine  
[name]  
[name]

[contact]  
[contact]  
Email: [contact]

Fax should state "Urgent Serious Adverse Event" on cover page.

All other AEs not fulfilling the criteria of immediate reporting must be recorded on the Case Report Form. This AE information will be collected on a regular basis during the clinical trial. Considering that the study drugs have already been tested in several hundreds of patients and that the study is not a double-blinded one, a Local Safety Monitor is not needed.

### **7.1.4 Reporting of adverse events**

For all adverse events identified, an adverse event report form will be completed.

For each possible adverse event identified and considered as **serious**, a serious adverse event notification form will be completed.

The following information will be recorded for all adverse events:

- 1) Study randomization number
- 2) Date of birth
- 3) Sex
- 4) Description of event
- 5) Date of event onset
- 6) Date event reported
- 7) Severity of the event
- 8) Study medication including start/stop dates
- 9) Relationship of the event to study medication
- 10) Is the event serious?
- 11) Initials of the person reporting the event
- 12) Was the event episodic or intermittent in nature?
- 13) Outcome of adverse event
- 14) Action taken
- 15) Date event resolved.

A severity grading scale, based on toxicity grading scales developed by the WHO and the National Institutes of Health, Division of Microbiology and Infectious Diseases, will be used to grade severity of all symptoms, physical exam findings, and haemoglobin results (see Appendix I). Any new event, or an event present at baseline that is increasing in severity, will be considered as an adverse event.

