#### Late Clinical Failure (LCF):

- (i) Development of danger signs or severe malaria after Day 3 in the presence of parasitaemia, (See Appendix V for the criteria of severe malaria/danger signs).
- (ii) Presence of parasitaemia and fever on any day from Day 4 to Day 28, without having previously meet the criteria of ETF.

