### **3.6 Statistical analysis**

Since the trial has been powered for equivalence at each site, interim analyses will be undertaken for each of the sites separately. Interim analyses will be undertaken by the trial statistician and presented to the DSMB every 6 months during recruitment while safety monitoring will be continuous. A detailed analysis plan will be drawn up prior to the first interim analysis.

For each analysis, both an intention-to-treat, a per-protocol and a CACE approach will be adopted. Patients in each treatment group in each site will be described separately with respect to baseline characteristics. The clinical importance of any imbalance will be noted though statistical tests of significance will not be undertaken.

For the analysis at each site, and for the primary outcomes relating to treatment failure, the relative treatment effect will be summarised in terms of the risk difference and associated confidence interval for each pairwise combination of treatments.

For the combination of data across sites, a meta-analytic approach will be employed. The six pairwise comparisons of treatments will be undertaken, stratified by site. Heterogeneity due to patient-level and site-level characteristics will be investigated. Finally, all data will be entered into a regression model and a network meta-analytic approach adopted.

If appropriate, logistic regression will be used to examine the effect of prognostic factors on the primary outcome. Tests of interaction between baseline characteristics and treatment will be kept to a minimum.

Adverse events will be grouped according to a pre-specified side-effect coding system and tabulated. The number (and percentage) of patients experiencing each adverse event will be compared across treatment groups. The number (and percentage) of occurrences of each adverse event will also be compared across treatment groups.

Every effort will be made to minimise the amount of missing data in the trial. However it is realistic to assume a priori that missingness may be informative. Whenever possible, information on the reason for missing data will be obtained. Sensitivity analyses, including imputation, will be undertaken to assess the robustness of the conclusions to the missing data.

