**Table A. Guidelines for Grading Patient Symptoms.**

|                                          | Grade 1
MILD                                                                                         | Grade 2
MODERATE                                                                       | Grade 3
SEVERE                                                                                           | Grade 4
LIFE THREATENING                                                                                 |
|------------------------------------------|-----------------------------------------------------------------------------------------------------------------|---------------------------------------------------------------------------------------------------|---------------------------------------------------------------------------------------------------------------------|---------------------------------------------------------------------------------------------------------------------|
| Subjective fever in the past 24 h | N/A                                                                                                             | Present (Yes)                                                                                     | N/A                                                                                                                 | N/A                                                                                                                 |
| Weakness                          | Mild decrease in activity; For children – weak, but still playing                                               | Moderate decrease in activity; For children – weak, and playing limited                           | Not participating in usual activities; For children – not playing                                                   | Prostration                                                                                                         |

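### Signs of late clinical failure can count as new adverse events, so the all-cause safety comparison is partly mixed with efficacy

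*Protocol*

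**What the plan says.** **Failure.** Section 3.2 gives late clinical failure two limbs. One is "Development of danger signs or severe malaria after Day 3 in the presence of parasitaemia". The other is "Presence of parasitaemia and fever on any day from Day 4 to Day 28", provided early failure has not already occurred. Fever is axillary temperature of at least 37.5 °C in the early-failure definition and in the inclusion criteria (section 3.9). Late parasitological failure is defined by a temperature below that value.

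**Adverse events.** Section 7.1.1 covers any untoward occurrence "which does not necessarily have a causal relationship with this treatment", including any "symptom or disease temporally associated with the use of a medicinal product, whether or not considered related to the medicinal product". Section 7.1.4 adds the counting rule, "Any new event, or an event present at baseline that is increasing in severity, will be considered as an adverse event", and refers to Appendix I for grading. Table C there makes 37.5–37.9 °C Grade 1. Table A lists "Subjective fever in the past 24 h" with a single grade (Grade 2).

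**Comparison.** Section 2 makes safety part of the main objective and says that the incidence of events will be compared between arms. Section 3.6 says: "The number (and percentage) of patients experiencing each adverse event will be compared across treatment groups", and says the same of the number of occurrences. Neither section limits this by relationship to drug, slide result or date of recurrence. Section 3.3 sets 28 days of adverse-event monitoring for each active follow-up.

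**The concern.** The same clinical episode can enter the analysis twice, once as a treatment failure and once as one or more graded adverse events such as fever, vomiting, anorexia or weakness. If it is severe malaria leading to hospital admission, it also meets a seriousness criterion in section 7.1.3.

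The arms could plausibly differ in symptomatic recurrence. Section 1.1 describes chlorproguanil and dapsone as rapidly eliminated and lumefantrine as slowly eliminated, and Table 1 lists several high-transmission sites. A tolerability difference in the all-cause table could then partly restate the efficacy result, and the table as specified would not show how much. The safety and efficacy parts of the main objective would not be fully separate evidence.

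**Working it through.** **Step 1. Does a late clinical failure meet the adverse-event rule?**

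- *Danger signs or severe malaria after day 3.* Both are exclusion criteria at entry (section 3.9), so when they appear later they are new.
- *Fever with parasitaemia in a child enrolled on history of fever alone with a normal temperature.* The raised temperature is a new Table C finding.
- *Fever with parasitaemia in a child who was febrile at entry.* It counts if its grade exceeds the baseline grade. At an equal or lower grade it counts only if fever returning after resolution is read as new. Section 7.1.4 does not settle this.
- *Subjective fever.* Table A has one grade, so it cannot increase in severity. If it was present at baseline, it counts only on the new-event reading.
- *Recurrence without fever.* This is parasitological failure and creates no fever event.

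Some late clinical failures are therefore certainly adverse events, and others depend on how each of the ten sites reads the rule.

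**Step 2. How large could the effect be?** The protocol states no rates for these quantities, so all three are assumptions:

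- *b*: proportion of children with a fever event for other reasons, equal in both arms (0 to 20%).
- *L*: proportion with late clinical failure (2% v 4%, 2% v 7%, 3% v 10%).
- *f*: share of those failures recorded as a new fever event (0, 0.5, 1).

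A child who already has a fever event is not counted twice, so

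P(fever event) = b + (1 − b) · L · f

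and the gap between two equally toxic arms is (1 − b) · (L₂ − L₁) · f.

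Example with b = 5%, L = 2% v 7%, f = 1: 0.05 + 0.95 × 0.02 = 6.9% against 0.05 + 0.95 × 0.07 = 11.7%. The gap is 0.95 × 0.05 = 4.8 points.

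Gap in percentage points with f = 1:

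| Late clinical failure | b = 0 | b = 5% | b = 10% | b = 20% |
|---|---|---|---|---|
| 2% v 4% | 2.0 | 1.9 | 1.8 | 1.6 |
| 2% v 7% | 5.0 | 4.8 | 4.5 | 4.0 |
| 3% v 10% | 7.0 | 6.7 | 6.3 | 5.6 |
| 5% v 5% | 0 | 0 | 0 | 0 |

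With f = 0.5 every entry halves. With f = 0 every entry is zero.

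**Step 3. Scale.** The largest direct comparison is DHAPQ v AL. Table 1 shows both drugs at 8 sites, and 8 × 170 = 1360 per arm, as section 3.1 states. There a 1.6-point gap is 0.016 × 1360 ≈ 22 children and a 7-point gap is 0.07 × 1360 ≈ 95 children. For orientation, section 3.5 says the combined studies can detect major adverse events at a frequency of 1–2%. That figure concerns major events, so it is only a loose benchmark for fever.

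**The case against.** **An adverse event is not a toxicity finding.** A reader might infer that the protocol counts recurrent malaria as drug toxicity. It does not. The definition carries no causal claim, and section 7.1.2 requires a five-level relationship rating that allows the child's illness as the cause. Events are also compared term by term, so fever appears as fever. This stands against the stronger reading. However, the comparison in section 3.6 does not use the rating, and the rating is made in an open-label trial.

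**Not every late clinical failure qualifies.** A reader might also infer that each one is automatically a new event. Step 1 shows that this is not fixed by the text, because fever or a history of it is present at entry and the rule is silent on signs that return. Nor is fever needed for the first limb. This stands.

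**The direction is not certain.** It may be tempting to say that the drug with more reinfections is penalised. Afebrile recurrences add no fever event, and recrudescences contribute as well as reinfections. Active follow-up stops at failure (section 4.4), which shortens event observation in the arm with more failures and works the other way. This stands, and it is a second route by which failure affects the event counts.

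**No inference hangs on it.** The synopsis rules out formal testing of adverse events. Section 3.6 does not repeat that, but it names no test either. The point therefore concerns how a descriptive table will be read.

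**The rates are assumed.** Section 3.5 expects efficacy of at least 90%. If that includes reinfections, 10% late clinical failure uses the whole allowance before any other failure is counted, so the upper row is an extreme case.

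**The tables may be settled elsewhere.** The analysis plan and the coding system are not shown and may separate these events. The recording rule in 7.1.4 is different, because it is an instruction to sites and belongs in the protocol.

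**Conclusion.** The concern holds in a limited form. The protocol's adverse-event rule and its failure definition overlap in threshold and time window, with no exemption for malaria, and the stated comparison is all-cause. With equal toxicity, an arm with more symptomatic recurrences could show more fever and malaria-symptom events. The excess is roughly 0 to 7 points under the assumed rates, and zero if returning fever is not counted as new or if failure rates are equal. The claims that every late clinical failure is an adverse event, or that recurrence is recorded as toxicity, go beyond the text. The point deserves a clarification and one extra presentation of the data. It is not grounds for abandoning the all-cause comparison.

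**What to change.** 1. **Section 7.1.4:** state whether a sign or symptom that returns after resolution is a new event, so that all ten sites record alike. Keep recording all events.
2. **Section 3.6 and the synopsis:** keep the all-cause table. Flag events that belong to an episode meeting the treatment-failure definition, meaning events recorded as signs of that episode with onset between the last negative slide and the failure visit, or on the day of that visit. Report the between-arm comparison with and without flagged events.
3. **Serious adverse events:** list severe malaria at failure separately within that table.

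Replacing the all-cause comparison with one censored at recurrence is debatable and is not needed here.

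**Cost.** Two wording changes and a derived flag. Slide dates and event onset dates are already collected. The item list in 7.1.4 has nothing linking an event to a malaria episode, so a pre-stated list of terms or one tick-box would be needed. The downside is small: a true drug reaction that starts with the recurrence moves to the flagged table, where it is still reported, and it remains in the all-cause table.

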#### ***7.1.5 Length of follow-up for adverse events***

**AEs presenting during the active follow-up period:** A patient still experiencing an AE at the end of the active follow up, i.e. at day 28 will be managed as follows:

- If the AE has been detected and reported before the last visit and
  - it is mild (Grade 1), the patient will be managed according to good medical practice and the active follow up will be stopped. The end date for the AE will be recorded as Day 28.
  - Its grade is more than, the patient will be followed until the AE resolves, improves, or stabilizes.
- If the AE is new, the AE will be reported and the patient will be followed until the AE resolves, improves, or stabilizes.

#### ***7.2 Laboratory Evaluations***

Blood samples will be properly labelled with patients' initials, randomisation number, protocol number, the study day and the date the sample is taken. Haematology and Clinical chemistry assessments will be performed locally at sites.

All laboratory results will be reported in Standard International Units or in conventional units.

##### ***Haematology and Blood Chemistry Tests***

Haemoglobin, red blood cells count, total white blood cell count, differential count, total bilirubin, ALAT, creatinine.

Blood samples collected on filter paper for PCR genotyping will be analysed at the Institute of Tropical Medicine, Antwerp, Belgium. Sample will be collected according to standard operating procedures.

#### ***Abnormal Laboratory Test Results***

The Investigator will mark in the CRF the laboratory values out of normal ranges (the biochemistry results will be specific to each site) and will indicate those of clinical importance. These will be considered as AEs, and the proper AE reporting procedure should be followed by the Investigator.

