## 3. TRIAL DESIGN

### 3.1 Study Design

This is a multi- centre, randomized, open label, multi-armed study involving 10 investigational centres that will enrol 5100 patients, 510 per site, 170 per arm. The 4 combinations will be tested and compared in different countries, with different malaria transmission and resistance characteristics (Table 1). A three-arm trial maximises the amount of information collected and, at the same time, keeps the individual studies manageable.

The total number of patients treated by each study treatment will be between 1700 (DHAPQ) and 1020 (AQ+AS and CDA). For the comparisons between treatment arms, the highest number of patients per arm will be 1360 (DHAPQ vs AL), and the lowest 340 for the comparison between AQ+AS and CDA. This is slightly different from what had been planned in the proposal submitted to the EDCTP. The Rwandan collaborators have requested not to test AQ+AS on the ground that this combination will not be used as first or second line treatment. Indeed, resistance to AQ in Rwanda is already substantial, particularly in the site of Rukara. This is why the arm AQ+AS has been replaced by DHAPQ.

The main justification for not performing a double-blind study is the requirement to use the double-dummy technique requiring placebos for 3 arms drugs per site, resulting into a treatment schedule which would be very laborious for the patient. In order to ensure concealment of treatment allocation and avoid other biases, the following requirements will be assured:

- 1 The randomization list will be generated prior the beginning of the study. Treatment allocation will be concealed until the completion of the screening and the final recruitment of the patient (see section 3.10);
- 2 The interpretation of the PCR reading will be blinded/masked with regard to the treatment allocation of the patients (see section 3.9);
- 3 An independent Data Monitoring Board will review all efficacy and safety data (see section 13.2).

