## **14. ETHICAL ISSUES**

AQ+AS and AL have been successfully used for the treatment of falciparum malaria in Phase III studies though the former in a non-coformulated form. AL is widely used to treat uncomplicated malaria in Africa. DHAPQ has been used for several years in Asia, including safety studies in children. Recent trials in Rwanda and Peru (initiated and followed up by the ITM, Belgium) do not show any specific safety problem^8. The combination is well tolerated. Chlorproguanil-dapsone has been used in young children, it is well tolerated and most of the serious adverse events recorded were more likely to be disease-related than drug-related. Dapsone is known to cause methaemoglobinaemia and haemolysis (especially in G6PD deficiency). Clinically significant increases in methaemoglobin were not seen in SP-treated patients, but were observed in 7% of those given chlorproguanil-dapsone (all mild cases and 1 moderate case, all of limited duration). None of the children showed dyspnoea, the main symptom of high methaemoglobinaemia, and no action was required by attending physicians. Severe hemolysis is of concern because it is a feature of falciparum malaria, making it difficult to identify cases of drug-induced haemolysis. G6PD-deficient children in the chlorproguanil-dapsone group were more likely than similar patients in the SP group to have a  $\geq 2\text{g/dL}$  Hb drop. However, by day 14 Hb values in both groups had been restored to baseline. Larger Hb falls after treatment with CD than after SP have already been reported. There is no reason to think that the addition of artesunate will increase such risk. Nevertheless, children receiving CDA will be carefully monitored and Hb tested every day until day 3 after treatment. If needed, blood transfusion can be rapidly done in all sites where CDA is tested. Moreover, the recruitment of children having an Hb  $\geq 7\text{g/dL}$  guarantees that, even if there is a drop, it will not reach life-threatening values.

The study will be presented for ethical clearance to the local ethical committees where the study is carried out and to the corresponding committees of the northern institutions directly involved in a specific site. Prior to the start of the project, the study will be explained to the communities involved. Written informed consent will be obtained from the guardians for all children before entering the study.

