**TABLE D. Guidelines for Grading of Laboratory Abnormalities**

|                           | Grade 1
MILD | Grade 2
MODERATE | Grade 3
SEVERE | Grade 4
LIFE-
THREATENING |
|---------------------------|-------------------------|-----------------------------|---------------------------|------------------------------------------|
| Haemoglobin (g/dL) | 9.0 – 9.9               | 7.0 – 8.9                   | 5.0 – 6.9                 | < 5.0                                    |

Reference – The Harriet Lane Handbook, 15th edition, 2000†

Reference – WHO Toxicity Grading Scale for Determining the Severity of Adverse Events

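### For haemoglobin, the protocol gives a grade rule and a clinical-importance rule for adverse-event status; they disagree, and the second is applied by investigators who know the arm

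*Protocol*

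**What the plan says.** Three sections of the protocol bear on when a laboratory result is an AE.

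- Section 7.1.1 defines an AE as an unfavourable sign "that could include a clinically significant abnormal laboratory finding".
- Section 7.1.4 applies the Appendix I severity scale to symptoms, physical findings and haemoglobin results, and then states: "Any new event, or an event present at baseline that is increasing in severity, will be considered as an adverse event". It asks for no judgement of importance.
- Section 7.2, under Abnormal Laboratory Test Results, has the investigator mark out-of-range values in the case report form and says that he or she "will indicate those of clinical importance. These will be considered as AEs". It gives no numerical threshold.

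Section 7.2 lists the tests as "Haemoglobin, red blood cells count, total white blood cell count, differential count, total bilirubin, ALAT, creatinine". Appendix I Table D is titled "Guidelines for Grading of Laboratory Abnormalities", but its only row is haemoglobin: grade 1 is 9.0–9.9, grade 2 is 7.0–8.9, grade 3 is 5.0–6.9 and grade 4 is below 5.0 g/dL.

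Section 3.1 describes a "randomized, open label, multi-armed study involving 10 investigational centres". Of the assessments, it masks only the PCR reading. Sections 1.1 and 14 say that dapsone is known to cause haemolysis, and Section 14 adds that "children receiving CDA will be carefully monitored and Hb tested every day until day 3 after treatment". Section 3.6 compares the number and percentage of patients with each AE, and the number of occurrences, across treatment groups. The synopsis adds that AEs will not be formally tested.

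**The concern.** An investigator with a falling haemoglobin in front of them has two rules that can give different answers. One is mechanical and rests on the grade. The other rests on opinion, held by someone who knows the treatment and has been told by the protocol to expect haemolysis with one of the drugs.

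Section 2 makes the comparison of AE incidence between arms part of the main objective, and Section 13.2 lets the monitoring board stop arms on the basis of what it reviews. If sites settle the conflict differently, or settle it differently for CDA than for its comparators, the haemoglobin AE counts partly reflect who was flagged and not only what happened. Suspicion of CDA could raise its count. Attributing falls to malaria, which Section 14 says is hard to tell apart from drug-induced haemolysis, could lower it. Pooling sites would not remove flagging that depends on the arm.

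**Working it through.** **1. The rules side by side, for haemoglobin.** The grades are from Table D. Children may enter with haemoglobin of 7.0 g/dL or more (Section 3.9), so some start at grade 1 or 2.

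| Change (g/dL) | Table D grade | AE under 7.1.4? | AE under 7.2? |
|---|---|---|---|
| 10.0 to 9.9 | none to 1 | yes | only if judged important |
| 8.9 to 7.0 | 2 to 2 | no | possible, if judged important |
| 13.0 to 10.0 | none to none | no | possible, if judged important |

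The first row is an AE by grade that judgement may discard. The other two, falls of 1.9 and 3.0 g/dL, are missed by grade and may be caught by judgement. Neither rule contains the other.

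**2. How much the grade rule depends on the starting value.** Take starting values from 7.0 to 13.0 g/dL in steps of 0.1, which gives 61 values.

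- A fall of 1.0 g/dL worsens the grade from 10.0–10.9 (10 values), 9.0–9.9 (10) and 7.0–7.9 (10), so 30 of 61.
- A fall of 2.0 g/dL worsens it from 10.0–11.9 (20), 9.0–9.9 (10) and 7.0–8.9 (20), so 50 of 61.

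This counts grid points. It does not weight them by how often children have each value.

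**3. Other laboratory tests.** Section 7.1.4 names haemoglobin and no other laboratory test, and Table D grades nothing else. For red and white cell counts, bilirubin, ALAT and creatinine, Section 7.2 stands alone and agrees with Section 7.1.1. No second rule contradicts it.

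**4. What arm-dependent flagging could do.** The protocol gives no flagging rates and no rate of haemoglobin worsening, so every rate here is an assumption. CDA and dihydroartemisinin-piperaquine share six sites (Table 1), so n = 6 × 170 = 1,020 per arm. Assume the same true worsening rate in both arms.

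- Recorded AE rate = true rate × probability of being flagged.
- SE = √[p₀(1−p₀)/n + p₁(1−p₁)/n] and z = (p₁−p₀)/SE.
- Chance that a nominal two-sided 5% comparison is significant ≈ Φ(z − 1.96).

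| True rate | Flagged, comparator v CDA | Recorded AE rate | Ratio | z | Chance |
|---|---|---|---|---|---|
| 20% | 50% v 60% | 10% v 12% | 1.2 | 1.44 | about 30% |
| 20% | 50% v 70% | 10% v 14% | 1.4 | 2.79 | about 79% |
| 20% | 50% v 80% | 10% v 16% | 1.6 | 4.05 | about 98% |
| 5% | 50% v 60% | 2.5% v 3.0% | 1.2 | 0.69 | about 10% |
| 5% | 50% v 70% | 2.5% v 3.5% | 1.4 | 1.32 | about 26% |
| 5% | 50% v 80% | 2.5% v 4.0% | 1.6 | 1.91 | about 48% |

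For the first row, SE = √[(0.0900 + 0.1056)/1,020] = 0.01385 and z = 0.02/0.01385 = 1.44. Exchange the flagging rates and the sign reverses. No AE test is planned, so the last column is only a yardstick for how visible a spurious gap might be.

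**The case against.** The best defence is that clinical judgement is the protocol's own AE definition. Section 7.1.1 speaks of clinically significant laboratory findings and Section 7.2 applies that. Section 7.1.4 sits under reporting and could be read as saying how to grade something already called an event. This reading is possible, but nothing in Section 7.1.4 says so. It names haemoglobin results and then makes new or worsening events AEs outright. The word "These" in Section 7.2 could even refer to all out-of-range values, which would be a third rule. The conflict for haemoglobin stands.

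Other parts of the defence limit the point and should be accepted:

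- Measured haemoglobin change on days 3, 7, 14 and 28 is a separate secondary endpoint (Section 3.3) and does not depend on flagging. It does not name the day 1 and 2 values added at CDA sites, and it does not repair the AE tables.
- Section 14 mentions daily testing for CDA children only, but the notes to Figure 1 apply the day 1 and 2 tests to all three arms at those sites. Any bias enters through flagging, not sampling.
- An independent board reviews the safety data, and AEs are only described. Descriptive counts can still mislead the board and readers.

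A reader might infer three stronger things that the protocol does not support. The first is that the conflict covers every laboratory test; it covers haemoglobin only. The second is that a haemoglobin fall becomes an AE only when judged important; Section 7.1.4 is a second route. The third is that the haemolysis concern is shown to drive AE rates by arm; the text shows only that it could.

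**Conclusion.** The point holds for haemoglobin. Sections 7.1.1 and 7.2 rest AE status on clinical importance with no threshold, Section 7.1.4 with Table D rests it on grade, and worked values show disagreement in both directions. That conclusion needs no assumption beyond the plain reading of Section 7.1.4.

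The consequence is a risk and not a demonstrated bias. Because investigators know the arm and know the concern about CDA, haemoglobin AE counts could be distorted by arm or by site, upwards or downwards. The assumed scenarios give recorded-rate ratios of 1.2 to 1.6 with no true difference, but those ratios are simply the ratios of the flagging rates chosen. The analysis of measured haemoglobin is untouched. The inconsistency should be corrected; it does not undermine the trial's safety assessment as a whole.

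**What to change.** 1. Reconcile Sections 7.1.1, 7.1.4 and 7.2 so that one stated rule governs when a haemoglobin result is recorded as an AE. This belongs in the protocol, because it decides what sites write down.
2. For the between-arm comparison, tabulate haemoglobin worsening by program from the recorded values, as any increase in Table D grade from day 0, identically in all arms. Keep the investigator's clinical-importance flag as a separate descriptive field.
3. For bilirubin, ALAT and creatinine, where measured (the notes to Figure 1 say not at all sites), show recorded values and out-of-range shifts by arm beside the investigator-flagged AEs. Do not restrict this to children in range at day 0, since that would drop those already abnormal who worsen.

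The 2 g/dL fall mentioned in Section 14 is a cited study's result and is not offered in the protocol as an AE criterion, so it should not be imported as one. Falls within a grade remain visible through the measured haemoglobin endpoint.

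The cost is a short text change, one programmed derivation from haemoglobin values already collected, and a longer list of low-grade haemoglobin events, including trivial ones such as 10.0 to 9.9 g/dL.
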